Building on the promising research that has supported the effects of character strength interventions on adolescent mental-health outcomes, our team has focused on developing and testing a simple, scalable, low-stigma, and low-cost intervention called Shamiri (Kiswahili for “thrive”) for Kenyan adolescents [20–22]. The Shamiri intervention includes three empirically supported brief character strength interventions: growth mindset [23–27], gratitude [28–30], and value affirmation [31, 32], which were iteratively adapted through co-design with and feedback from local stakeholders [20, 33] to be appropriate for use in Kenyan high schools. Shamiri is a group-based intervention delivered in naturalistic school settings by lay providers who are recent high school graduates without formal training in mental health [20, 21]. We tested the Shamiri intervention in a randomized controlled trial (RCT) with 51 Kenyan adolescents with clinically elevated depression and/or anxiety symptoms; youths assigned to Shamiri reported significant improvements in depression and anxiety symptoms, academic performance, and perceived social support from friends when compared to youths in an active study skills control group of equal duration [16]. In a well-powered replication (*N* = 413) [21], we found that youths assigned to the Shamiri intervention reported significantly greater improvement in depression and anxiety symptoms than youth in the control group. Effects lasted until the 7-month follow-up period [33]. Besides this, both RCTs showed that the Shamiri intervention was feasible and acceptable for Kenyan youths.

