### Sample size {14}

We conducted a power analysis using Optimal Design, a statistical simulation software which can estimate sample size for randomized controlled trials assessed using multi-level (i.e., mixed effects) models [74]. In Optimal Design, we estimated the required sample size for a person-randomized trial with six-time repeated measures (baseline, midpoint, post, 1-month follow-up, 3-month follow-up, 6-month follow-up, and 9-month follow-up). Additionally, for each outcome measure, we have four contrasts of primary interest (each intervention condition compared to the control), thus, using a conservative *p* value correction, we would divide the typical alpha value of .05 by four and get a *p* value threshold for significance of .0125. Finally, we assumed that we are interested in detecting a minimum post-treatment effect size of .3. We selected this value for the following reasons: 1) it is slightly lower than the effect sizes found in most previous trials of Shamiri, which range from .32–.83 at the latest follow-up points [3, 20, 33, 34], which will allow us to detect potentially smaller effects of the individual component interventions, and to detect effects in a universal sample, and 2) a standardized effects size of .3, which is considered small to medium, remains clinically meaningful and important in our view, whereas a change smaller than that may not be as clinically meaningful. Given these parameters, we found that a sample of 515 students would be needed to conduct a two-group trial with a power of .80. So, for this five-group trial, we multiplied that by 2.5, to get a final target sample size of 1288 students. Because in a past trial with 7-month follow-up there was a high dropout rate during follow-up of up to 40% [33], we will initially invite 2147 students to the sessions, assuming that around 40% of them will drop out prior to the sessions or during the follow-up period.

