Primary models will include all five groups, using the control group as the contrast group. Secondary models will include the four intervention conditions, using the full Shamiri intervention as the contrast group. Significant (*p* < .05 with a Holm-Bonferroni correction to account for four comparisons within each model) time × condition interactions will indicate that one condition produced significantly steeper improvements than another condition across the time included in the analyses. As described above and per recommendations outlined in past literature [78], the Holm-Bonferroni correction will be applied at a family-wise level (i.e., to account for multiple group comparisons on each outcome), rather than at a study-wise level.

Additionally, for all pairwise contrasts (including those comparing active interventions to each other) on all primary and secondary outcomes, effect sizes will be calculated as mean gain scores, to compare change within the various intervention and control groups.

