### Interim analyses {21b}

No interim analyses will be conducted during the intervention sessions, which are only 4 weeks long. Additionally, we do not anticipate systematic harm to participants due to study participation, thus we do not have study stopping guidelines in place. For individual participants who clinical supervisors deem as having serious risk of harm to self or others, the local expert clinician could decide, in collaboration with the school administration, to withdraw the participant from the trial and instead provide more intensive individual support. See supplemental emergency protocol documents for more. However, the outcomes from 2-week midpoint, 4-week endpoint, and 1-month follow-up will most likely be analyzed prior to those at 3-month, 6-month, and 9-month follow-up, and will accordingly be reported separately. This is because of the large number of groups and outcomes, which would likely prohibit reporting all in one manuscript.

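### The deciding test is a time × condition slope, a poor test of an early gain from a 4-week intervention; its result turns on an unstated time coding and on which of two windows is confirmatory

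*Protocol article*

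**What the plan says.** Protocol article, Statistical methods {20a}: every primary and secondary outcome is analysed with a linear mixed model for the time × condition interaction. A random intercept per participant is planned, and random slopes are to be tried and dropped if they overfit. The decision rule is that significant "time × condition interactions will indicate that one condition produced significantly steeper improvements than another condition across the time included in the analyses", with a Holm-Bonferroni correction for four comparisons per model. Mean gain scores are added as effect sizes. No test at a named time point is planned, and the coding of time is not stated.

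Sample size {14}: "we assumed that we are interested in detecting a minimum post-treatment effect size of .3", with a "value threshold for significance of .0125". The result is that "a sample of 515 students would be needed to conduct a two-group trial with a power of .80", giving a "final target sample size of 1288 students".

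Interim analyses {21b}: "the outcomes from 2-week midpoint, 4-week endpoint, and 1-month follow-up will most likely be analyzed prior to those at 3-month, 6-month, and 9-month follow-up", with the two sets reported separately.

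Background {6a}, on the earlier replication trial: "Effects lasted until the 7-month follow-up period".

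**The concern.** Treatment is over by week 4, but the visits fall at about 0, 0.5, 1, 2, 4, 7 and 10 months from baseline. The rule speaks of steeper improvement and counts one comparison per active arm, which points to a single linear time term. Over this schedule the late visits dominate such a slope. A gain that arrives by week 4 and stays is fitted as a shallow line. One that partly fades is fitted as nearly flat, and one that fades fully as a negative slope.

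The sizing text describes a post-treatment difference, which is a different quantity from a rate of change. The analysis window is left as whatever time is included, and two windows are planned. An arm that helped early could therefore be reported as ineffective, or as worse than control, depending on how time is coded and which window is taken as decisive.

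**Working it through.** **The plan's own figure.** Two-sided alpha .0125 gives z = 2.498; power .80 gives z = .842.

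- Two-means formula: N = 4(2.498 + .842)²/.3² = 496 (499 with noncentral F). This does not match 515.
- Linear growth-rate formula: N = 4(2.498 + .842)²(1 + V)/.3², with V = 12/[(M−1)M(M+1)], equally spaced visits and an assumed variance ratio of 1. For M = 7, V = 12/336 = .036 and N = 513 (517 with noncentral F), close to 515. For M = 6, N is 524 (528). The protocol says six measurements but lists seven.
- 515 × 2.5 = 1287.5, rounded to 1288; 1288/.6 = 2147 invited. Both reproduce.

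So .3 may have been entered as a slope effect, although the text calls it post-treatment. The match rests on the assumed variance ratio and does not prove it.

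**Power of the slope test.** From the protocol: 515/2 = 257.5 per arm, alpha .0125, effect .3, the visit schedule. Assumed: two-sided test, SD 1, within-person correlation ρ = .3/.5/.7, complete data, no clustering. The slope is b = Σ(t − t̄)y/S with S = Σ(t − t̄)², and y is the arm-minus-control difference at each visit. Its standard error is SE = √[2((1−ρ)/S + τ²)/257.5], where τ is the person-slope SD (0 for a random intercept only). Power is Φ(b/SE − 2.498).

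Three profiles reach .15 at week 2 and .3 at week 4. One then holds at .3; the others fall linearly to .15 or to 0 at the last visit.

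- Months, all visits: t̄ = 3.5, S = 84.5. Holds: b = 1.5/84.5 = .0178 per month (.18 over 10 months). Half-faded: .175/84.5 = .0021. Fully faded: −1.15/84.5 = −.0136 (−.14 over 10 months).
- Visit number 0–6: t̄ = 3, S = 28. Holds: 1.2/28 = .043 per visit. Half-faded: .5/28 = .018. Fully faded: −.2/28 = −.007.
- Months, first four visits: t̄ = .875, S = 2.1875. Holds: .31875/2.1875 = .146 per month.

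Example, months, ρ = .5, effect holds: SE = √[2(.5/84.5)/257.5] = .0068; b/SE = 2.62; power Φ(.12) = .55.

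Power in favour of the intervention, at ρ = .3/.5/.7:

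| Profile | All visits, months, τ = 0 | All visits, months, τ = .05 | All visits, visit number, τ = 0 | To 1-month follow-up, months, τ = 0 |
|---|---|---|---|---|
| Holds at .3 | .39/.55/.81 | .29/.38/.54 | .72/.87/.99 | .66/.83/.98 |
| Fades to .15 | .01/.01/.02 | about .01 | .11/.16/.29 | .60/.78/.96 |
| Fades to 0 | about 0 | about 0 | about .001 | .53/.71/.93 |

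In the last row the full-follow-up slope points to control. With months and τ = 0 the chance that control is significantly steeper is Φ(|b|/SE − 2.498) = .21/.31/.54. With visit number it is only .02/.03/.04.

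**Alternatives at the same n and alpha.** A baseline-adjusted difference at one visit has SE = √[2(1−ρ²)/257.5]. If the true difference there is .3, power is .86/.92/.99. The baseline-adjusted average of the five visits from week 4 has SE = √[2((1+4ρ)/5 − ρ²)/257.5]. If .3 holds, power exceeds .99 throughout.

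**If benefit really grows linearly to .3 at the last visit.** The slope test (months, τ = 0) has power .89/.97/>.99. A 9-month contrast has .86/.92/.99. The five-visit average sees .03 × 24/5 = .144 and has .60/.60/.74.

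**The case against.** The strongest case is that the protocol fixes neither the window nor the coding, and an article may leave coding to the analysis plan. In the early window, or with visit-number coding over all visits, a held effect has power around or above the planned .80 for ρ of .5 and higher. That stands. A reader might infer that the trial cannot detect an early, sustained .3 effect; the document does not support this as a general statement. It is true of months coding, up to a correlation of about .5 with a random intercept only, or across the range with τ = .05.

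The 515 may itself be slope-based, so sizing and analysis may agree and only the wording be loose. The sizing section never names week 4, and it supports .3 by effects at the latest follow-ups of earlier trials. A reader might infer that a 4-week contrast is what the sample was sized for; the text does not say so.

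The fading profiles are assumptions. The background reports that effects lasted, which fits an early plateau but does not describe one, and nothing in it suggests fading. Means and SDs at every visit and gain scores will also be reported, so an early benefit would be visible, though not through the deciding test.

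Two windows might be thought to give each null contrast an 8–10% false-positive chance. That figure needs testing at .05 in both windows, which Holm allows only at its last step. At .0125 it is about 2.2–2.4%.

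Finally, grades are measured in three terms. With equal spacing, the slope is half the pre-to-post change, so this distortion does not arise.

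What survives is that the stated rule tests a rate of change, the sizing text names a post-treatment effect, and {21b} plans two windows without saying which decides.

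**Conclusion.** The point holds in this form: for the questionnaire outcomes, the deciding test suits an early gain poorly, and the conclusion can turn on choices the protocol leaves open. For a held .3 effect at ρ = .5 with a random intercept, coding alone moves full-follow-up power from .55 (months) to .87 (visit number). For a half-faded effect it is at most about .30 under either coding, against .60–.96 in the early window with time in months. For a fully faded effect the two windows point in opposite directions.

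These figures rest on SD 1, 257.5 analysed per arm, two-sided .0125, correlation .3–.7, complete data, no clustering and, for the last two cases, hypothetical profiles. They do not show that the trial is underpowered for every early effect. If time were categorical, the slope objection would fall away, although the wording on steeper improvement points to a line.

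**What to change.** In {20a}, model time as categorical, or piecewise (baseline to week 4, then follow-up), with adjustment for baseline. Name one confirmatory arm-versus-control contrast per outcome, either at a stated time or as the average of the post-treatment visits. The choice is the sponsor's and should fit its stated interest in longer-term effects; a week-4 contrast is not the only candidate. In {21b}, say which report carries that contrast and that the other is estimation or maintenance only. In {14}, say whether .3 is a difference at that time or a slope effect. Give grades their own contrast, such as the post-intervention term adjusted for the pre-intervention term.

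The cost is wording and a few more model coefficients. The downside is some loss of power if benefit truly grows linearly to 9 months: small for a 9-month contrast (.86–.99 against .89 to over .99), larger for the five-visit average (.60–.74).

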**Methods:**

In this five-arm randomized controlled trial, we will test each of the intervention components (growth mindset, gratitude, and value affirmation) against the full Shamiri Intervention and against a study skills control intervention. Students (*N*_planned_ = 1288) at participating secondary schools who are interested in participating in this universal intervention will be randomized in equal numbers into the five groups. The students will meet in groups of 8–15 students led by local high school graduate lay providers. These lay providers will receive a brief training, plus expert supervision once a week throughout the intervention delivery. Multi-level models will be used to compare trajectories over time of the primary outcomes (depressive symptoms, anxiety symptoms, academic performance, and wellness) and secondary outcomes in each intervention group to the control group. Multi-level models will also be used to compare trajectories over time of the primary outcomes (depressive symptoms, anxiety symptoms, academic performance, and wellness) and secondary outcomes of participants in the single-element interventions compared to the full Shamiri Intervention. Finally, effect sizes (calculated as mean gain scores) will be used to compare all groups on all measures.

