## Statistical methods

### Statistical methods for primary and secondary outcomes {20a}

Outcome measures will only be analyzed if they demonstrate internal consistency within the full sample at baseline, defined as an alpha value of .70 or above [75]. For those outcome measures that pass this threshold, all main analyses of primary and secondary outcomes will follow an intent-to-treat approach, meaning that all participants who consent, are randomized into the groups, and complete baseline measures will be included in all analyses (see 20c below for more about plans for handling missing data).

For all analyses of primary and secondary outcomes, we plan to use linear mixed effects models to model time × condition interaction with a random intercept for participant ID to allow for individual variation at baseline. We plan to control for age and sex in all models of primary and secondary outcomes. Age will be included because older adolescents report increased psychosocial stress and thus greater risk of mental illness [3]. Similarly, sex differences in anxiety and depression are widely documented in adolescents including Kenyan adolescents [3, 76]. Additionally, the authors will test more complicated random effects structures which reflect the hierarchical structure of the data, including random effects for groups within group leaders, crossed random effects for schools and group leaders, and for participants in groups. We will also test adding a random slope for participant ID and for school; however, these added random effects may result in overfitting, which would reduce the generalizability of our findings. If this is the case, we will select a more parsimonious model with a simpler random effects structure. These variables (group leader, school, and group) will also be tested as covariates rather than random effects in the model, and final model selection will be done taking into account both overfitting warnings and Akaike Information Criterion (AIC) [77].

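### Pairwise effect sizes are defined as mean gains within groups, although a contrast between arms needs a between-arm difference, and they are the only stated comparison of one single element with another

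*Protocol article*

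**What the plan says.** The hypothesis tests come from mixed models. In the Protocol article, section {20a}, "we plan to use linear mixed effects models to model time × condition interaction with a random intercept for participant ID", and "We plan to control for age and sex in all models of primary and secondary outcomes". Two sets of contrasts follow: "Primary models will include all five groups, using the control group as the contrast group", and "Secondary models will include the four intervention conditions, using the full Shamiri intervention as the contrast group". Holm-Bonferroni is applied within each outcome.

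Effect sizes are then added "for all pairwise contrasts (including those comparing active interventions to each other) on all primary and secondary outcomes". Their definition is that "effect sizes will be calculated as mean gain scores, to compare change within the various intervention and control groups". The abstract repeats it with a between-group purpose: "effect sizes (calculated as mean gain scores) will be used to compare all groups on all measures".

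The sample-size section {14} is built on "detecting a minimum post-treatment effect size of .3". It calls this value standardized and treats smaller changes as possibly less meaningful clinically. The sections on the choice of comparators {6b} and on the study skills control both expect that control to reduce symptoms somewhat.

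**The concern.** The article picks a measure of change inside one arm and assigns it to comparisons between arms. For seven of the ten pairs this does limited harm, because a model contrast stands beside the gain score. For the three element-vs-element pairs nothing else is stated.

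Those three pairs bear on a stated purpose. The background asks whether some elements help more than others, and the Discussion asks which intervention is most effective and links the answer to dissemination. If the comparison rests on within-arm gains, a reader sees figures that mix the element's effect with change common to all arms. There is also no stated way to set them against the .3 that the article uses as its mark of clinical meaning.

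**Working it through.** **1. The plan's own figures.** Inputs from section {14}: effect .3, alpha .05/4 = .0125, power .80, two-group total 515. Two-sided testing is assumed.
- Normal formula: 4(2.498 + 0.842)²/.3² = 495.6, or 496 in total. The exact t test gives 500.
- Repeated-measures slope formula: the same quantity times (1 + ratio/SS), where SS is the sum of squared deviations of equally spaced occasions and ratio is within-person variance over slope variance. With ratio 1 (assumed; the article gives neither variance), seven occasions (SS = 28) give 513 and six (SS = 17.5) give 524.
- So 515 is reproduced closely. Then 515 × 2.5 = 1287.5, i.e. 1288, or 257.6 per arm, and 1288/.6 = 2147. Nothing below changes these figures.

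**2. Which pairs have a model contrast.** Five arms give 5 × 4/2 = 10 pairs.
- Control as reference: 4 pairs.
- Shamiri as reference, control excluded: 3 pairs.
- Remaining: 10 − 7 = 3 pairs (growth vs gratitude, growth vs values, gratitude vs values). The gain-score effect sizes are their only stated comparison.

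**3. A within-arm gain against a between-arm difference.** Let control gain c baseline SDs and let an arm beat control by .3. The arm's own gain is c + .3. The article gives no value for c, so these are assumptions:

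| Control gain c | Arm's gain | Between-arm difference |
|---|---|---|
| 0 | .3 | .3 |
| .2 | .5 | .3 |
| .4 | .7 | .3 |

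If c = .3, an arm with no advantage over control also shows a gain of .3. The gain alone cannot be read against the .3 target.

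**4. A difference in gains: does the scale match?** This depends on the divisor, which is not named.
- Divided by the baseline SD, a difference of .3 stays .3.
- Divided by the SD of gains, with equal SDs at both times and baseline-to-follow-up correlation r, it becomes .3/√(2(1 − r)): .25 (r = .3), .30 (.5), .39 (.7), .47 (.8). The article gives no r; this range is assumed.

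**5. How coarse an element-vs-element comparison is.** With 257.6 per arm, no clustering and no further loss (all favourable assumptions), the standard error of a simple difference in gains, in baseline SDs, is √(2 × 2(1 − r)/257.6): .104, .088 and .068 at r = .3, .5 and .7. The 95% half-widths (1.96 × SE) are .20, .17 and .13. Against a threshold of .3, these pairs need a difference with an interval, not two gains side by side.

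**The case against.** The sentence applies to pairwise contrasts, so it can fairly be read as the difference between two arms' mean gains. On that reading shared change cancels, and under individual randomisation the difference is unbiased by design. With complete data and time treated as categorical, a random-intercept model gives the same point estimate. The effect sizes are also an addition to the model tests, and an article may leave the divisor, time points and intervals to a full analysis plan.

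Much of this stands. It does not remove the mismatch in what the article does state: the purpose given is to compare change within groups, while the use given is to compare groups. Choosing that measure is not a detail left for later.

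A reader might go further in four ways that the document does not support.
- **That components will be ranked on raw gains.** No section says so.
- **That the figures are necessarily unadjusted or completer-only.** Section {20a} includes all randomised participants with baseline data in all analyses, and section {20c} imputes missing data. Neither section says how the gain scores are computed.
- **That the figures are off the .3 scale.** This cannot be established, since no divisor is named for either quantity and some choices make them coincide.
- **That gain scores lose precision against a baseline-adjusted comparison.** That comparator is an analysis of covariance, which the article does not plan; its models treat baseline as a repeated outcome.

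**Conclusion.** The point holds in a limited form. The article defines its pairwise effect sizes as within-group gains, which do not fit a between-arm contrast as worded, and three of ten pairs have no other stated comparison. The gains are not shown to be on the scale of the .3 target. If reported within arm, they exceed the contrast with control by whatever control gains; the article expects that to be an improvement but gives no size.

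The count of pairs rests on the article alone. The illustrations of size rest on assumed control gains and correlations. The tests against control and against Shamiri, the multiplicity rule and the sample size are untouched. This is a cheap improvement, not a threat to the main inference. With dropout of around 40% allowed for in section {14}, tying the effect sizes to the models on imputed data would also rule out their being taken from completers only.

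**What to change.** In section {20a} and in the abstract's Methods, define each pairwise effect size as the between-arm difference in change estimated from the planned mixed model on the imputed data, at named time points, divided by the pooled baseline SD, with a 95% confidence interval pooled over imputations. Name the three element-vs-element pairs explicitly; they are linear combinations of coefficients in the five-arm model. Keep within-arm gains as descriptive columns, and state that the .3 in section {14} is read on the same scale.

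Cost: about one sentence in each of the two places and a little more analysis work on models already planned. There is no change to data collection, sample size or the planned tests.
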